### Trial status

The official study start date was 1 April 2015. Recruitment to the feasibility trial began on the 1 June 2015 with the first patient entered into the study on 5 June 2015.

## Ethics and dissemination

### Informing potential trial participants of possible benefits and known risks

The stroke research officer will provide the patient and their consultee (if appropriate) with a verbal explanation of the trial and written patient information sheets, ensuring that the participant has sufficient time to consider participating or not. The CRN research officer will answer any questions that the participant has concerning study participation.

### Obtaining informed consent from participants

Trained stroke research officers will obtain written informed consent from patients willing to participate in the trial. The informed consent form will be signed and dated by the participant before they enter the trial and before they undergo any interventions (including history taking) related to the study. Patients who are unable to sign their name because the stroke has affected their dominant hand and they are unable to sign a legible signature with their non-dominant hand will be asked to point to a box within the consent form and a witness will sign to state that the patient wished to give informed consent to participate in the study.

An ‘aphasia friendly’ version of the information sheets and consent form will be available for those with communication difficulties. Such aphasia friendly information sheets and consent forms have been used in previous stroke trials by the study team.

Patients who lack the mental capacity to consent to participate in the study will be recruited after consultation with their next of kin or nominated carer. Consultee advice will be obtained from the patient's relative or close friend who would know the patient's wishes. Capacity is a situation-specific assessment and the CRN staff and clinical stroke team have had training in assessing capacity. Those participants who lack capacity will be considered for recruitment to the main feasibility trial only and not participation in the patient and carer interviews.

Irrespective of patients’ mental capacity, verbal or gestured agreement will be sought prior to ES treatment, and objections will be respected. If a participant becomes distressed by the ES treatment, it will be stopped.

Participants who lack capacity to provide informed consent will not be recruited to the patient and carer interview part of the study, but their nominated carer may opt to be interviewed about their experience of supporting someone without capacity to participate in the trial.

Owing to the early delivery of ES within 72 h poststroke, it may be that obtaining informed consent from the patient is not possible due to communication and/or cognitive difficulties. In these circumstances, we will obtain consultee consent. However, if during the intervention period the patient regains their communication and/or cognitive function, we will obtain informed consent from the patient at that time.

### Study withdrawal

It will be explained to the potential participant or their consultee that entry into the study is entirely voluntary and that treatment and care of the participant will not be affected by their decision. Participants or their consultee will be informed that they can withdraw from the study at any given point and that this will not affect their future care. Participants may be withdrawn from the trial either at their own request or at the discretion of the investigator. The participants will be made aware that this will not affect future care. Participants will be made aware (via the information sheet and consent form) that should they withdraw, the data collected to date cannot be erased and may still be used in the final analysis.

Participants may discontinue their allocated intervention or withdraw from the study for the following reasons:
Withdrawal of consent,Changes to their health status preventing their continued participation.

Enrolled participants who withdraw and were not yet randomised will be replaced (though the withdrawn participant will keep their trial ID). Participants who withdraw after randomisation will not be replaced.

### Data protection and confidentiality

All trial staff and investigators will endeavour to protect the rights of the trial's participants to privacy and informed consent, and will adhere to the Data Protection Act 1998. The CRF will only collect the minimum required information for the purposes of the trial. CRFs will be held securely in a locked filing cabinet with access limited to the trial staff. Computer held data including the trial database will be held securely on a dedicated web server and will be encrypted and password protected. Participant confidentiality will be ensured by utilising identification code numbers. Individual participant medical information obtained as a result of this study are considered confidential and disclosure to third parties is prohibited.

Access to the CRFs shall be restricted to those personnel approved by the principal investigator and recorded on the Trial Delegation Log. The full data set will be restricted to the Trial Management Group, Independent Trial Steering Consultant and Sponsor. On completion of the study and following dissemination of the findings, secondary anonymised data will be available on request.

### Research governance and the conduct of the trial

The trial is being conducted in accordance with the ethical principles that have their origin in the Declaration of Helsinki 1996, the principles of Good Clinical Practice, and the Department of Health Research Governance Framework for Health and Social Care 2005.

### Dissemination of research findings

As this is a feasibility study, the main dissemination strategy will be after the ensuing trial. The findings from this study will be disseminated through study reports, through publications in academic peer reviewed journals, and conference presentations. The results will be communicated to the participants and involved stroke unit staff in the form of a letter thanking them for their involvement and support of the study, along with a lay summary of the findings and plans for future research.

### Clinical trials authorisation

Clinical trials authorisation is not required.

### Trial management and regulatory issues

This study is being hosted by Nottingham University Hospitals NHS Trust and coordinated by the University of Nottingham (the research sponsor). The principal investigator ([name]) will manage the day-to-day running of the study. The Trial Management Group will meet quarterly throughout the trial to discuss progress, including recruitment, withdrawals, treatment compliance, clinical issues and dissemination plans. As this is a feasibility study, the funder does not require a formal Trial Steering Committee or Data Monitoring Committee. However, an independent Trial steering Consultant will monitor and supervise the progress of the study towards its interim and overall objectives; concentrate of progress of the trial, adherence to the protocol and consideration of new information of relevance to the research question; provide advice on all appropriate aspects of the trial; and agree proposals for substantial protocol amendments. This independent monitor will audit the core trial processes and documents

Any potential modifications to the protocol will be discussed and agreed by the Trial Management Group, Trial Steering Consultant and the research Sponsor. Permission for a formal amendment to the protocol will then be sought from the Research Ethics Committee who granted the original ethical approval for the study. The local NHS Research and Development office will then be notified of any approved amendments.

Table 1 shows all items from the WHO trial registration data set.

**Table 1 BMJOPEN2015010079TB1:** All items from the WHO trial registration data set

Data category	Information
Primary registry and trial identifying number	ISRCTN Registration ISRCTN16489086
Date of registration in primary registry	15/01/2015
Secondary identifying numbers	ClinicalTrials.gov NCT02324634
Source(s) of monetary or material support	Monetary support: Department of Health funding from the NIHR RfPB programme (PB-PG-1013-32034) Material support: NeuroTrac Rehab devices used for the intervention were donated by Verity Medical Ltd
Primary sponsor	University of Nottingham
Secondary sponsor(s)	Nottingham University Hospitals NHS Trust
Contact for public queries	[name] (principal investigator) [contact]
Contact for scientific queries	[name] (principal investigator) [contact]
Public title	Early Electrical Stimulation to prevent Complications to the Arm Post-Stroke—a feasibility study (ESCAPS)
Scientific title	Early electrical stimulation to the wrist extensors and wrist flexors to prevent the post-stroke complications of pain and contractures in the paretic arm—a feasibility study
Countries of recruitment	England, UK
Health condition(s) or problem(s) studied	Stroke: prevention of post-stroke complications (eg, pain and contractures) in the upper limb
Intervention(s)	ES applied to the wrist extensors and wrist flexors for 30 min, twice a day, 5 days a week, for 3 months The ES will be set to deliver a 450 μs pulse at a frequency of 40–60 Hz (as per patient convenience). The intensity of the current will be increased to produce an alternating contraction of the flexors and extensors using a flex-hold-extend-hold pattern. A single stimulation and hold cycle will last 20 s and this will be cyclically repeated for 30 min Control group will receive usual care only and will not receive any ES treatment
Key inclusion and exclusion criteria	Inclusion criteria: Confirmed clinical diagnosis of first disabling stroke event affecting the upper limb Aged >18 years Impaired arm movement and strength (NIHSS arm subscore >0) resulting in reduced function, caused specifically by the stroke Exclusion criteria: Previous history of stroke affecting their upper limb Peripheral nerve injury/existing orthopaedic condition affecting the upper limb; fixed contractures at the elbow, wrist or fingers; malignancy in the area of the ES electrode placement; or epilepsy Cardiac pacemaker or similar implanted device Pregnancy Undiagnosed pain or skin conditions (not related to the stroke)
Study type	Feasibility RCT (single centre) Interventional Allocation: randomised Masking: unblinded (for practical reasons during the feasibility trial but in any subsequent pilot and definitive trials the outcomes assessor will be blinded)
Date of first enrolment	June 2015
Target sample size	40
Recruitment status	Recruiting
Primary outcome(s)	Pertain to the feasibility aims of the study: Feasibility of the trial design (12 months)—recruitment rates: number/per cent of participants recruited within 72 h post-stroke; time post-stroke that participants received their first treatment; recruitment strategy: number/per cent of patients screened, number/per cent eligible and approached, number/per cent who consented, number/per cent excluded after screening; completion rates: number/per cent of participants who completed the intervention; number/per cent of participants who received ES twice a day, 5 days a week while in hospital, and number/per cent who continued with the treatment regime after discharge. Mean, minimum and maximum number of ES treatments that participants received during the 3-month intervention period; recruitment of patients lacking mental capacity to consent for themselves: consultee consent rates (number/per cent of patients unable to give informed consent, and number consented by a consultee, number of consultees who declined consent) Tolerability (12 months)—proportion of participants who withdraw or decline intervention; records of interventions declined and why Integrity of the study protocol (12 months)—measured by examining how many participants are able to complete the study, per cent of missing data, and per cent of people who completed each of the outcome measures at 3-month, 6-month and 12-month follow-up, calculation of the cost of running the study
Key secondary outcomes	NIHSS score (0, 3, 6, 12 months)—neurological outcome and degree of recovery Barthel ADL Index score and modified Rankin score (0, 3, 6, 12 months)—independence (functional ability) in basic daily activities SPIN (0, 3, 6, 12 months)—pain in the affected arm Muscle contractures (reduction in range of movement and spasticity; 0, 3, 6, 12 months)—muscle contractures will be monitored by measuring muscle activity during assessments using Biometrics equipment ARAT (0, 3, 6, 12 months)—arm function SS-QOL (0, 3, 6, 12 months)—stroke-related quality of life EQ-5D (0, 3, 6, 12 months)—health status Patient resource use (cost) questionnaire (0, 3, 6, 12 months)—a measure of resource use and health-related costs CSI (0, 3, 6, 12 months)—carer strain NEADL (0 months)—premorbid functional state MoCA (0 months)—cognitive status at baseline

ADL, activities of daily living; ARAT, Action Research Arm Test; CSI, Caregiver Strain Index; ES, electrical stimulation; EQ-5D, EuroQoL-5D; ISRCTN, International Standard Randomised Controlled Trial Number; MoCA, The Montreal Cognitive Assessment; NEADL, Nottingham Extended ADL; NHS, National Health Service; NIHR, National Institute for Health Research; NIHSS, National Institute for Health Stroke Scale; RCT, randomised controlled trial; RfPB, Research for Patient Benefit; SPIN, Scale of Pain Intensity; SS-QOL, Stroke Specific Quality of Life Scale.

### Adverse events

The occurrence of an adverse event as a result of participation is not expected and no adverse event data will be collected. The ES device itself is not under investigation and these devices have already passed extensive safety testing and are considered safe for use by patients with a range of conditions including stroke. Such devices are currently used in some areas of clinical practice on an ad hoc basis. The manufacturer's advice will be followed with regard to excluding patients who have a contraindication (eg, implanted cardiac pacemaker, epilepsy, pregnancy, malignancy in the area of the electrode placement).

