Neuromuscular ES is a safe and harmless treatment for use in patient groups without the contraindications of uncontrolled epilepsy, pregnancy and those fitted with cardiac pacemakers. Metallic implants, cancerous lesions and risk of brittle bones around the stimulation site or the joint being treated are also contraindications. National clinical guidelines^2^ recommend routine use of ES for treating ‘foot drop’,^3^ but there is insufficient evidence to support the routine use in upper limb rehabilitation.^2^ Recently, Rosewilliam *et al*^17^ recruited 90 patients with no upper limb function 6 weeks after stroke and concluded that those who received ES of wrist extensors showed improved wrist extension, strength and grip. Secondary analysis concluded ES prevented the development of pain and deterioration in contractures.^4^

The ESCAPS study evaluates the feasibility of conducting a multicentre randomised controlled trial (RCT) of the efficacy and cost-effectiveness of early, intensive ES to prevent wrist joint deformities/contractures, weakness and upper limb pain after stroke. Qualitative components will explore barriers and facilitators to protocol adherence and clinical practice implementation.

The national clinical guidelines for stroke recommend that occupational therapists should aim to ‘re-educate’ the arm of patients who have reduced arm movement following stroke, by providing repetitive task training. This is inappropriate for many patients with stroke who do not have upper limb mobility. Treatment with ES does not require active movement; therefore, it could benefit patients who have severe to moderate arm function deficits.

This RCT is the first to study ES of flexors and extensors. Reciprocal stimulation of flexors and extensors will simulate the natural stretching movement and can be more effective in the prevention of contractures than stimulation of extensors alone. Flexor stimulation has been shown to reduce spasticity rather than being a contraindication.^18^
^19^

In order to prevent deconditioning of the forearm muscles, there is a need to initiate treatment within 72 h of stroke. Premature discontinuation of therapy may reduce any therapeutic effect. No extended trials have been conducted, so it is important to establish compliance and attrition rates.

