### Exclusion criteria

Exclusion:
An existing chronic upper limb condition (eg, peripheral nerve injury);Cardiac pacemaker;Pregnancy;Epilepsy;Undiagnosed pain or skin conditions (not related to the stroke).

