### Outcome measures

The primary outcomes relate to the feasibility outcomes of the study.
Feasibility of the trial design:
Recruitment rates: number/per cent of participants recruited within 72 h post-stroke; time post-stroke that participants received their first treatment;Recruitment strategy: number/per cent of patients screened, number/per cent eligible and approached, number/per cent who consented, number/per cent excluded after screening;Completion/attrition rates: number/per cent of participants who completed the intervention;Compliance/adherence to treatment protocol: number/per cent of participants who received ES twice a day, 5 days a week while in hospital, and number/per cent who continued with the treatment regime after discharge. Mean, minimum and maximum number of ES treatments that participants received during the 3-month intervention period;Consultee consent rates: number/per cent of patients unable to give informed consent, and number/per cent consented by a consultee, number of consultees who declined consent;Tolerability: number of participants who withdraw or decline intervention; records of interventions declined and why;Integrity of the study protocol: measured by examining how many participants are able to complete the study, number/per cent of missing data, and number/per cent of people who completed each of the outcome measures at 3-month, 6-month and 12-month follow-up, calculation of the cost of running the study; analysis of the qualitative interview and focus group data. The secondary outcomes relate to clinical outcome measures. Demographic characteristics (age, gender, ethnicity and socioeconomic status), stroke characteristics (date, type and side of stroke), cognitive status (MoCA^22^) and premorbid function state (Nottingham Extended ADL (NEADL)^24^) will be collected at baseline.

Participants will complete the following assessments at 0, 3, 6 and 12 months:
Neurological outcome (NIHSS^20^ score);Independence in daily activities (Barthel ADL Index score^25^ and modified Rankin Scale (mRS)^26^
^27^);Pain in the affected arm (Scale of Pain Intensity (SPIN)^28^);Muscle contractures/muscle activity (Biometrics EMG equipment);Arm function (ARAT^21^);Stroke-related quality of life (Stroke Specific Quality of Life Scale (SS-QOL))^29^;Health status (EuroQol-5D (EQ-5D)^30^);Patient resource use questionnaire;Carer strain (Caregiver Strain Index (CSI)^31^) will be completed by the participant's nominated carer.

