### Data analysis

Data will be statistically summarised/analysed using SPSS, and MathCad will be used to extract measures related to spasticity and contractures. Analyses will cover the following:
Total patients recruited within 72 h of stroke event; average length of time post-stroke when patients received first treatment.Total patients screened, eligible and approached, consented, and excluded after screening.Total patients who completed the intervention; number who completed 3-month, 6-month and 12-month follow-up assessments.Total participants receiving ES per protocol (PP); mean, minimum and maximum number of ES treatments received during 3-month intervention period; qualitative patient/carer interview data, and ES machine's memory which records number of sessions and duration.Total patients unable to give informed consent; number consented by consultee; number of consultees who declined.Recruitment and attrition rates, number of patients lost to follow-up and reasons.Quality of health economic data between assessment points especially 6–12 months regarding completeness. Cross referencing of data against medical records where possible. Sensitivity of the EQ-5D in measuring outcome. Combined cost and outcome analysis to determine potential cost-effectiveness of ES verses usual care.Thematic analysis will be used to identify themes representative of patient experience of treatment, and the experience of carers with the application of the ES device.

As the sample size is small and a method of minimisation is used, we propose to estimate effect size (using the Cohen's d and the 95% CI) for the main study measures that are interval level data. The OR (and the 95% CI) will be estimated when data are dichotomous. When measures are ordinal, nominal relative risk ratios will be used to present all forms of adverse events.

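### The protocol rules out collecting adverse event data but plans relative risks for all adverse events, so that analysis cannot be run and no adverse event rate can be reported in either arm

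*Protocol article*

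**What the plan says.** Two sections of the protocol article deal with adverse events directly.

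- **Adverse events:** "The occurrence of an adverse event as a result of participation is not expected and no adverse event data will be collected". The reasons given are that the device is not itself being investigated, that it has passed safety testing, and that patients with a contraindication will be excluded on the manufacturer's advice.
- **Data analysis:** "When measures are ordinal, nominal relative risk ratios will be used to present all forms of adverse events".

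Outcome measures sets the context: "The primary outcomes relate to the feasibility outcomes of the study". One of these is defined as "Tolerability: number of participants who withdraw or decline intervention; records of interventions declined and why". Pain in the affected arm (SPIN) is a secondary outcome at 0, 3, 6 and 12 months. Data analysis also lists the number lost to follow-up, with reasons.

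Contraindications and exclusions appear in four places.

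- **Introduction:** after epilepsy (if uncontrolled), pregnancy and pacemakers, "Metallic implants, cancerous lesions and risk of brittle bones around the stimulation site or the joint being treated are also contraindications".
- **Exclusion criteria:** after chronic upper limb conditions, "Cardiac pacemaker;Pregnancy;Epilepsy;Undiagnosed pain or skin conditions".
- **Table 1:** adds, among others, "fixed contractures at the elbow, wrist or fingers; malignancy in the area of the ES electrode placement; or epilepsy".
- **Adverse events:** gives pacemaker, epilepsy, pregnancy and malignancy near the electrodes as examples.

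**The concern.** One section says the data will not exist and another commits to analysing them. This is not a detail that a condensed article leaves to a fuller document: the article states positively that collection will not happen.

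The rationale also answers a different question. Earlier testing of the device speaks to the device. The trial tests a regimen: reciprocal stimulation of wrist flexors and extensors, started within 72 h of stroke, twice a day on 5 days a week for 3 months. According to Intervention treatment, no therapist need be present after set-up, and patients or carers manage the treatment themselves after discharge where possible. The abstract presents this early use on both muscle groups as the first such study, and the Introduction notes that no extended trials have been done.

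At stake is what the feasibility trial can hand to the definitive one. An objective is to judge whether starting ES within 72 h is appropriate, and that judgement would be made without any count of harms. Events that are not recorded during follow-up cannot be recovered reliably afterwards.

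**Working it through.** The plan gives no adverse event figure to reproduce. The check sets the sections side by side and then asks what recording could deliver at this sample size.

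**1. Can the promised relative risk be computed?** A relative risk needs (events in ES / n in ES) ÷ (events in control / n in control). Under the Adverse events section, neither event count is recorded, so the ratio is undefined. It also cannot be read as 0/n in each arm, because nobody looks for events. The Data analysis sentence is garbled and may have lost punctuation between its ordinal/nominal clause and the relative risks, but on any reading it commits to presenting adverse events.

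**2. What would other planned data show?**

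| Event | Captured by a listed outcome? |
|---|---|
| Arm pain | Yes, as a SPIN score in both arms, without attribution to treatment |
| Event leading to withdrawal or loss to follow-up | Partly, through the stated reason, in both arms |
| Event leading to a declined ES session | Yes, through the tolerability records |
| Skin reaction or fall that does not stop treatment | No |

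**3. What could about 20 per arm deliver if events were recorded?** Inputs: 40 participants (Sample size) and 1:1 allocation (Study design), so 40 / 2 = 20 per arm. The event risks and counts below are illustrative assumptions; the document gives none.

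- Chance of seeing at least one event in the ES arm, 1 − (1 − p)^20:
  - p = 1%: 1 − 0.99^20 = 18%
  - p = 5%: 1 − 0.95^20 = 64%
  - p = 10%: 1 − 0.90^20 = 88%
- Exact upper limit after 0/20 events:
  - one-sided 95%: 1 − 0.05^(1/20) = 13.9%
  - two-sided 95%: 1 − 0.025^(1/20) = 16.8%
- Relative risk for 4/20 against 2/20:
  - RR = 4 / 2 = 2.0
  - SE of log RR = √(1/4 − 1/20 + 1/2 − 1/20) = √0.65 = 0.806
  - 95% CI = 2.0 × exp(±1.96 × 0.806) = 0.41 to 9.7

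Recording would probably reveal a common harm and would put a ceiling on the risk of an unseen one. It would not yield a useful between-arm ratio.

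**4. Do the contraindication lists agree?** Metallic implants, cancerous lesions and brittle bones are contraindications in the Introduction. None of the three is named under Exclusion criteria. Table 1 names malignancy at the electrode site, but neither metallic implants nor brittle bones by name. The Introduction limits epilepsy to the uncontrolled kind, and the other lists do not.

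**The case against.** The strongest reply is that this is a small feasibility study of an established device, safety is not among the stated objectives, and a relative risk from 20 per arm would be close to uninformative even with full collection. Nothing says the definitive trial will omit adverse event recording or rest on a no-harm finding from this one. The contradiction could also be removed simply by deleting the analysis sentence. All of this stands. It bears on how events should be summarised and on which remedy to choose. It does not make the two statements compatible.

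A reader might infer three stronger things that the document does not support.

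- **That tolerability cannot be reported.** It can. It is defined by withdrawals and declined treatment with reasons, and those are recorded.
- **That harms would surface only through a withdrawal or declined session, and only in the ES arm.** SPIN measures arm pain in both arms, and reasons for loss to follow-up cover the whole trial. Interviews with 10 intervention and 5 control participants and their carers may add something. These sources are indirect and incomplete, but they exist.
- **That patients with a contraindication would be randomised.** The Adverse events section commits to following the manufacturer's advice, and its list is by way of example. Table 1 also excludes existing orthopaedic conditions of the upper limb and implanted devices similar to a pacemaker, which plausibly cover part of the gap. What stands is that the lists differ.

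**Conclusion.** The point holds as a direct contradiction between the Adverse events and Data analysis sections. As written, the adverse event analysis cannot be run and no adverse event rate can be given for either arm. The device-safety rationale does not fill the gap, because the regimen is what is new. A skin reaction or fall that does not interrupt treatment is missed by every listed outcome.

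The conclusion rests on the text and needs no assumed event rate. The figures illustrate scale only and assume 20 analysed per arm: with recording, 0/20 events would bound the risk at 13.9% (one-sided 95%); without it, there is no bound. The mismatch between the contraindication and exclusion lists is a secondary point and does not carry the conclusion.

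**What to change.** 1. **Adverse events section.** Replace the statement that nothing will be collected with recording of a short prespecified set of events, including serious events and deaths, in both arms at the existing 3-, 6- and 12-month visits. Ask the same scripted questions in both arms, since the assessor is not blinded. The usage diary may supplement this in the ES arm, but only users of the device keep one, so diary-only events should be kept out of any comparison between arms.
2. **Data analysis section.** Replace the relative risks with counts and exact confidence intervals by arm, labelled descriptive.
3. **If events will not be collected,** delete the adverse event analysis and state plainly that safety is not assessed.
4. **Separately,** reconcile the contraindications in the Introduction and Adverse events sections with the exclusions in Exclusion criteria and Table 1. Which list is right is for the investigators to settle.

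The cost is one extra case report form page, slightly longer visits and an amendment. Under Trial management and regulatory issues, the amendment needs agreement from the Trial Management Group, the steering consultant and the sponsor, then permission from the ethics committee. Recruitment began in June 2015, so the report should state from what date events were recorded and for how many participants.
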